## Abstract

**Background:**

Autism spectrum disorder (ASD) and schizotypal disorder (SD) both have a heterogenous presentation, with significant overlaps in symptoms and behaviour. Due to elevated recognition and knowledge of ASD worldwide, there is a growing rate of referrals from primary health professionals to specialised units. At all levels of assessment, the differential diagnostic considerations between ASD and SD exert major challenges for clinicians. Although several validated screening questionnaires exist for ASD and SD, none have differential diagnostic properties. Accordingly, in this study, we aim to develop a new screening questionnaire, the schiZotypy Autism Questionnaire (ZAQ), which provides a combined screening for both conditions, while also indicating the relative likelihood of each.

**Methods:**

We aim to test 200 autistic patients and 100 schizotypy patients recruited from specialised psychiatric clinics and 200 controls from the general population (Phase 1). The results from ZAQ will be compared to the clinical diagnoses from interdisciplinary teams at specialised psychiatric clinics. After this initial testing phase, the ZAQ will be validated in an independent sample (Phase 2).

**Conclusions:**

The aim of the study is to investigate the discriminative properties (ASD vs. SD), diagnostic accuracy, and validity of the schiZotypy Autism Questionnaire (ZAQ).

**Trial registration:**

Clinical Trials, NCT05213286, Registered 28 January 2022, clinicaltrials.gov/ct2/show/NCT05213286?cond = RAADS&draw = 2&rank = 1.

**Supplementary Information:**

The online version contains supplementary material available at 10.1186/s12888-023-04690-3.

## Background

The psychiatric burden in people with Autism Spectrum Disorder (ASD) [1] is considerably higher compared to neurotypical individuals, with 70% experiencing at least one co-occurring psychiatric disorder and 40% exhibiting two or more psychiatric disorders [2]. In a clinical setting and at all levels of assessment, one of the most difficult differential diagnostic challenges is schizotypal disorder (SD), which shares considerable features with ASD both at the symptomatic level and in the diagnostic criteria (see Fig. 1). Thus, discriminating ASD from SD in a clinical setting is a time-consuming task and demands a high level of expertise of both disorders. An audit of 319 patient cases at our clinic (specialized unit for the assessment of ASD) from January-June 2019 showed that about 37% of the adults referred to our clinic for the assessment of ASD, did not meet diagnostic criteria. Of these, almost 40% were diagnosed on the schizophrenia spectrum (predominantly SD). To improve diagnostic accuracy, it is therefore not only pertinent but also necessary to investigate discriminating features between ASD and SD and to develop tools to aid clinicians in the assessment.

**Fig. 1 Fig1:**
[figure not shown]
Diagnostic criteria for Autism Spectrum Disorder (ASD) and Schizotypal Disorder (SD). The encircled criteria mark the highest degree of clinical overlap

### Autism spectrum disorder

ASD and SD historically and practically have been grounded in two different scientific traditions, which has had a significant impact on the way clinicians assess patients and how the diagnostic criteria have developed (see Fig. 2).

**Fig. 2 Fig2:**
[figure not shown]
Development of concepts and criteria (figure provided by [name])

ASD has its roots in the relatively young field of child and adolescent psychiatry, whereas SD comes out of a more than 100-year-old tradition and is primarily based on clinical presentations in adults. Consequently, professionals involved in assessment of ASD and SD often come from different backgrounds and make use of different diagnostic methods. The prevalence estimates of ASD display a high variability across nations worldwide. In most western countries the prevalence is estimated to be 1–2% [3]. Danish data suggest a prevalence of 1.65% or approximately 95,000 persons in Denmark [4]. The case identification and assessment of ASD is challenged by a high rate of comorbidity with depression (50%), anxiety (40%) and ADHD/ADD (40–60%) [5, 6]. The prevalence of comorbidity with SD has to our knowledge not been established. Nevertheless, some indications of the relation between ASD and SD can be estimated by looking at studies comparing ASD with psychosis or schizophrenia spectrum disorders (SSD). Sub-clinical psychotic symptoms occur frequently in ASD patients [7–9], and the prevalence of SSD in adults with ASD are in the range of 4–12% [5].

To aid in case identification of ASD, several screening questionnaires have been developed, including the Autism Spectrum Quotient (AQ) [10], the Ritvo Adult Asperger Diagnostic Scale Revised (RAADS-R) [11], and the Social Responsiveness Scale (SRS) [12]. Importantly, however, several studies indicate that such questionnaires do not differentiate well between autistic individuals and individuals with SSD [13, 14].

### Schizotypal disorder

SD is also a heterogeneous disorder with an estimated prevalence of 4.6% and a high rate of comorbidity [15, 16]. The diagnosis can be made if at least 4 out of 9 ICD-10 criteria are met (see Fig. 1). Although debated [17], SD is considered a crucial construct in the development of SSD [18]. Thus, early diagnosis is important for prognosis, as 25–48% of SD patients are prodromal and go on to develop SSD [17, 19]. The prevalence of comorbidity between ASD and SD, which is the main focus of this study, has to our knowledge not been described in any detail. However, the prevalence of ASD in individuals with SSD seems to be substantially increased relative to the general population, although estimates vary widely [20].

Several psychometrically robust questionnaires are available to assess features of and screen for SD. In adult populations these notably include the Schizotypal Personality Questionnaire Brief Revised (SPQ-BR) [21], the Oxford-Liverpool Inventory of Feelings and Experiences (O-LIFE) [22], the Multidimensional Schizotypy Scale (MSS) [23], the Cardiff Anomalous Perception Scale (CAPS) [24], and the Community Assessment of Psychic Experience (CAPE) [25]. In children, these notably include the Melbourne Assessment of Schizotypy in Kids (MASK) [26] and the Schizotypy Personality Questionnaire in Children (SPQ-C) [27], (see Table 2). To our knowledge, none of these have significant psychometric power to discriminate SD from ASD.

Given significant difficulties in discriminating between ASD and SD and the serious consequences that case misclassification can have for treatment and prognosis, we have sought to develop the schiZotypy Autism Questionnaire (ZAQ) to aid clinicians in the assessment of and discrimination between ASD and SD in adults at the case identification stage. A pilot version of this novel screening questionnaire ZAQ, containing 130 questions, has been developed at the Mental Health Centre, Capital Region of Copenhagen. This will be tested in 300 psychiatric patients and 200 healthy controls from May 2022 – April 2023, which constitutes Phase 1 of this study. Psychometric data analysis from this study will constitute the empirical foundation for the development of the final version of ZAQ. This final version, which pending statistical recommendations is expected to contain approximately 60 questions, will undergo subsequent validation in an independent sample (Phase 2).

## Methods

### Description of the creation of ZAQ

To construct the ZAQ, we first performed an exhaustive literature search to identify potential discriminating features between ASD and SD. Complementing the literature search, we interviewed three experienced clinicians who identified discriminating factors based on their clinical knowledge. Altogether, we identified 38 features which appeared to differentiate ASD and SD. These features constituted 11 subscales, subsumed under 6 subdomains (see Table 1). Identification of potentially discriminating features has been the primary focus. Once identified these features were grouped together into well-defined subscales. To present an overview, these subscales are grouped together in subdomains, highlighting the areas showing potential for discrimination [28, 29].

**Table 1 Tab1:** Summary of the domains, subdomain and subscales serving as the theoretical framework for ZAQ^a^

**Main ZAQ-domains**	**Subdomain**	**Subset of items on which responses between individuals with ASD or SD might differ**	**Subscales**	**Number of questions**
**Diagnostic criteria**	Autism	Stereotyped behavior, narrow interests, hyper-hyposensitivity to sensory stimuli	1. Steretyped behavior	14 questions
			2. Hypersensitivity + Narrow interest	11 questions
	Schizotypy	Self-disorders, hyper-reflexitivity, magical ideation, positive schizotypy	3. Self-disorders	17 questions
			4. Magical ideation + positive schizotypy	13 questions
			5. Disorganised schizotypy	5 questions
			6. Negative schizotypy	10 questions
**Clinical features**	Clinical trajectories	Time of onset of symptoms, childhood symptoms	7. Clinical trajectories and symptoms	19 questions
**Psychological theory**	Theory of Mind (ToM)	Inference of intentions of others, ToM performance, self-referential hypermentalisation, facial emotion perception	8. Theory of Mind	13 questions
	Local vs. global processing	Local vs. global processing, imagination and creativity, reading abilities, word interpretation, savant feature, apophenia	9. Local vs. global processing	8 questions
**Cognitive features**	Attention, memory	Selectivity of attention, selective memory/false memory, working memory performance	10. Cognition	12 questions
			11. Higher Cognitive Functions	9 questions

^a^Note: For a comprehensive account, see also references [28, 29]

Secondly, the research group identified several psychometrically-validated assessment and screening questionnaires for schizotypy and ASD (see Table 2). From this list of questionnaires, questions were extracted based on their clinical face validity, factor loadings from the validity studies of these questionnaires, and reliability scores (e.g., test–retest reliability). This process yielded approximately 950 questions (version 1 ZAQ).

**Table 2 Tab2:** Scales and questionnaires used in the development of the schiZotypy Autism Questionnaire (ZAQ)

Scales and Questionnaires							
**Scales/ Questionnaires**	**References for validation**	**Scales/ questionnaires**	**References for validation**	**Scales/ questionnaires**	**References for validation**	**Scales/ questionnaires**	**References for validation**
**Schizotypy**		**Theory of Mind**		**Autism Spectrum Disorder (ASD)**		**Cognitive features**	
**SPQ** Schizotypal Personality Questionnaire	Raine 1991 [30]	**TH.O.M.A.S** Theory of Mind Assessment Scale	Bosco et al. 2009 [31]	**RAADS-R** Ritvo Autism Asperger Diagnostic Scale-Revised	Ritvo et al. 2011 [11]	**WMS** Working Memory Scale	Vallat-Azouvi 2012 [32]
**O-LIFE** Oxford-Liverpool Inventory of Feelings and Experiences	Mason et al. 2005 [22]	**Self-referential Hinting Task**	Wastler & Lenzenweger 2019 [33]	**SRS** Social Responsiveness Scale	Constantino et al. 2003 [12]	**DFlex** Detail and Flexibility	Roberts et al. 2011 [34]
**MSS** Multidimensional Schizotypy Scale	Kwapil et al. 2018 [23]	**Strange Stories**	Happe 1994 [35]	**AQ** Autism Spectrum Quotient	Baron-Cohen et al. 2001 [10]	**DOSPERT** Domain Specific Risk Taking	Blais and Weber 2006 [36]
**CAPE** Community Assessment of Psychic Experience	Konings et al. 2006 [25]	**TAS-20** Toronto Alexithymia Scale	Bagby et al. 1994 [37]	**EQ** Empathy Quotient	Baron-Cohen & Wheelwright 2004 [38]	**CRT** Cognitive reflection task	Frederick 2005 [39]
**PAGE-R**	Fach et al. 2013 [40]	**ADI-r** Autism Diagnostic Interview-Revised	Lord et al. 1994 [41]	**RBS** Repetitive Behaviour Scale	Lam el al Aman 2007 [42]	**CAQ** Creative assessment questionnaire	Carson et al. 2005 [43]
**MASK** Melbourne Assessment of Schizotypy in Kids	Jones et al. 2015 [26]	**Self-disorders**		**SPQ** Sensory perception quotient	Tavassoli et al. 2014 [44]	**ARHQ** Adult Reading History Questionnaire	Lefly and Pennington 2000 [45]
**CAPS** Cardiff Anomalous Perception Scale	Bell et al. 2006 [24]	**EASE (Semi Structured)** Examination of Anomalous Self-Experience	Parnas et al. 2005 [46]				
		**SQuEASE6** Short Questionnaire 6 of EASE	Møller 2018 [47]				
		**IPASE** Inventory of Psychotic-Like Anomalous Self-Experiences	Cicero et al. 2019 [48]				

In a first round of evaluation of their face-validity, these 950 questions were presented to six experienced clinicians—each with extensive (+ 5 years) clinical knowledge in either ASD or SD and who were not associated with the research group. These clinicians assessed how their patients would answer these 950 questions. Importantly, questionnaires measuring schizotypy were assessed by clinicians with ASD experience and vice versa. This evaluation retained 195 questions (version 2 ZAQ). All items of the version 2 ZAQ then underwent a second round of evaluation by 5 autistic patients and 2 schizotypy patients. Of these 195 questions, judged on the basis of their unambiguity and clarity, the final 130 questions entering Phase 1 of the study were selected. The resulting subscales ranged from 5–19 items.

### Recruitment and testing

We have designed a multicenter, prospective, non-randomized experimental study, where adult patients will be recruited from May 2022 – April 2023. A group of 300 patients will be recruited from 2 outpatient clinics located at Mental Health Centre Copenhagen: 200 patients (see power calculation) will be recruited from the pool referred to the specialised clinic for diagnostic assessment of ASD at Mental Health Centre Copenhagen, and 100 patients will be recruited from the specialised psychosis clinic at Mental Health Centre with an SD diagnosis. Additionally, a group of 200 adults from the general population without a psychiatric diagnosis will be recruited as a control group. Inclusion and exclusion criteria are detailed in Table 3. The data will be collected on-line and managed through a secure server with full compliance with Personal Data Handling laws of Denmark.

**Table 3 Tab3:** Inclusion and exclusion criteria

**Inclusion Criteria: Patients 18–65 years (ASD and non-ASD psychiatric)**	**Exclusion Criteria: Patients (ASD and non-ASD psychiatric)**
WAIS-IV or Raven IQ > 85, no-clinical suspicion of intellectual disability and minimum 11 years of education	Insufficient Danish language skills
Completion of: - Clinical Assessment - Adult Asperger Assessment (AAA) - Psychopathology evaluation using DSM-5 - A conclusion based on multidisciplinary consensus	Acute psychiatric illness prompting departure/dismissal from the diagnostic assessment
Controls: Are matched with age, gender, marital status, number of children, and educational level	Controls: Concurrent or prior psychiatric diagnosis (self-report)

In all three outpatient clinics, the diagnostic assessment will be carried out as usual and will follow gold standard guidelines in their respective fields. The diagnostic assessment of ASD will be performed by clinicians who are not involved in the study. Using DSM 5, the assessment will be based on clinical interviews (minimum 4 h, including childhood history and differential diagnostic assessment) and supplemented by a semi-structured interview (Adult Asperger Assessment, AAA). Video recordings from AAA assessment and the clinical assessment will be presented at a multidisciplinary meeting, with at least 2 experienced clinicians, who will finalize the diagnostic conclusion. A schematic showing the flow of patients is depicted in Fig. 3. The result from this initial phase of the study will undergo psychometric analysis and items displaying adequate validity and discriminating power will be selected for the final ZAQ questionnaire (Phase 2).

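### The abstract counts 200 autistic patients, but the design recruits 200 people referred for ASD assessment, of whom the clinic's own audit suggests about 126 will have ASD

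*Protocol article*

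**What the plan says.** The Methods paragraph of the abstract reads: "We aim to test 200 autistic patients and 100 schizotypy patients recruited from specialised psychiatric clinics". On that wording both patient groups are defined by diagnosis, and together they account for all 300 patients.

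Recruitment and testing describes the larger group differently: "200 patients (see power calculation) will be recruited from the pool referred to the specialised clinic for diagnostic assessment of ASD". The smaller group is still defined by diagnosis: "100 patients will be recruited from the specialised psychosis clinic at Mental Health Centre with an SD diagnosis". The total is fixed: "A group of 300 patients will be recruited from 2 outpatient clinics located at Mental Health Centre Copenhagen". The eligibility heading in Table 3 covers patients both with and without ASD, and the Fig. 3 caption divides patients after clinical evaluation into ASD, SD and neither.

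The Background gives the only figure on what such referrals turn out to be. It describes "An audit of 319 patient cases at our clinic (specialized unit for the assessment of ASD) from January-June 2019" and reports that "about 37% of the adults referred to our clinic for the assessment of ASD, did not meet diagnostic criteria". Almost 40% of those non-ASD cases were on the schizophrenia spectrum, mostly but not all SD.

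The Power calculation section, cited for the 200, mentions n = 200 only as a rule of thumb for factor analysis. It then works with a combined clinical and non-clinical sample of 500.

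**The concern.** The same 200 people are described once as autistic patients and once as people referred to find out whether they are autistic. By the clinic's own audit, more than a third of such referrals do not have ASD. The abstract's figure is therefore not what the recruitment rule would deliver, and its two patient groups leave no place for the neither group in Fig. 3.

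This bears on the main comparison. The Outcome section hypothesises an AUC of at least 0.7 for ASD against SD, and also makes a claim about the positive predictive value of the cut-off. A predictive value depends directly on the mix of diagnoses. Anyone who takes group sizes from the abstract would start from the wrong mix.

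**Working it through.** **Totals that reproduce.** 200 + 100 = 300 patients; 300 + 200 controls = 500; 500/60 = 8.3, stated as 8:1. These stand.

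**The figure that does not.** Inputs: 200 referred patients (Recruitment and testing), 37% not ASD and almost 40% of those on the schizophrenia spectrum (Background).

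- ASD: 200 × (1 − 0.37) = 126.
- Not ASD: 200 × 0.37 = 74, the gap from the stated 200.
- Schizophrenia spectrum: 74 × 0.40 = 29.6, about 30. Not all of these are SD, so this is an upper bound for SD.
- The rest: 74 × 0.60 = 44.4, about 44. This is a lower bound for neither ASD nor SD.

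**Uncertainty in the rate.** The Wilson 95% interval for 63% with n = 319 is 57.6% to 68.1%; times 200, that is 115 to 136 ASD patients. As a wider assumed range, take a non-ASD share of 30% to 45%:

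- 30%: 140 ASD and 60 not ASD, of whom at most 60 × 0.40 = 24 SD and at least 36 neither.
- 45%: 110 ASD and 90 not ASD, of whom at most 90 × 0.40 = 36 SD and at least 54 neither.

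**Referrals needed for 200 confirmed ASD.** 200/0.63 = 317.5, so 318. With the 100 SD patients that makes 418 patients, against the stated 300.

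**Effect on AUC precision.** The Hanley-McNeil standard error is √{[A(1−A) + (n₁−1)(Q₁−A²) + (n₂−1)(Q₂−A²)]/(n₁n₂)}, with Q₁ = A/(2−A), Q₂ = 2A²/(1+A) and n₁ the positive class. At A = 0.70, Q₁ = 0.538 and Q₂ = 0.576. The result depends on which diagnosis counts as positive, so both are shown. The 95% half-width is 1.96 × SE.

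| ASD vs SD | SE, SD positive | Half-width | SE, ASD positive | Half-width |
|---|---|---|---|---|
| 200 vs 100 | 0.0333 | 0.065 | 0.0303 | 0.059 |
| 126 vs 100 | 0.0354 | 0.069 | 0.0343 | 0.067 |
| 126 vs 130 | 0.0325 | 0.064 | 0.0326 | 0.064 |

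At 126 vs 100 the half-width grows by about 0.004 (SD positive) or 0.008 (ASD positive). If all 30 spectrum cases joined the SD group, it would fall by about 0.002 or rise by about 0.004.

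**Effect on predictive value (illustration only).** The document gives no sensitivity or specificity. Assume both are 0.65 and leave out the neither group. The positive predictive value for ASD is then:

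- 200 vs 100: 130/(130 + 35) = 0.79.
- 126 vs 100: 81.9/(81.9 + 35) = 0.70.
- 126 vs 130: 81.9/(81.9 + 45.5) = 0.64.

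**The case against.** The strongest defence is that Table 3 requires a completed assessment and a multidisciplinary conclusion before a patient counts as included. The 200 could then be confirmed ASD cases drawn from the referral pool, which would agree with the abstract. That reading does not survive the rest of the text. The same table admits patients without ASD, Fig. 3 has a neither group, and with 100 of the 300 places going to the psychosis clinic only 200 remain for the ASD clinic, whatever the diagnosis.

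A second objection does stand as a caveat. The audit is from 2019, and the article does not say that its cases met the trial's IQ, education, language and completion criteria. The 126 is an expectation under an assumption, and should be presented with its range.

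Three stronger conclusions are tempting but not supported:

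- A reader might infer that about 126 ASD patients breach the n = 200 rule for factor analysis. The Power calculation section applies its sizing to the combined 500, not to each diagnosis.
- A reader might infer that a stated 2:1 ratio or a stated AUC precision is wrong. The article states neither, and it defers confidence in the AUC to the end of Phase 1.
- A reader might infer that the ASD-versus-SD comparison is seriously weakened. The precision loss is small and, if the ASD clinic's spectrum cases join the SD group, its direction depends on the choice of positive class.

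**Conclusion.** The point holds as a misstated group size. Under the recruitment rule as written, and if the audit rate carries over, the ASD group is about 126 rather than 200, an overstatement of about 74 patients. The range is 115 to 136 from audit sampling error and 110 to 140 over the wider assumed rates; neither comes near 200. At the audit rate, at most about 30 of the remainder would have SD and at least about 44 would have neither diagnosis, a group that the abstract's counts leave out. The cross-reference to the power calculation supports no ASD number.

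The consequences are limited. The 500 total and the 8:1 ratio hold if all participants enter the factor analysis, and the AUC half-width at 0.70 grows by no more than about 0.008. What matters most is that the size and mix of the diagnostic groups are stated wrongly in a study whose main question is the contrast between them.

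**What to change.** In the abstract and in Recruitment and testing, describe the 200 as patients referred for ASD assessment. Beside that, give the expected numbers as ranges, with the audit assumption stated: about 126 ASD (110 to 140), at most about 30 SD (24 to 36) and at least about 44 with neither (36 to 54). List the 100 SD patients from the psychosis clinic and the 200 controls separately.

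Base any later precision or predictive value for ASD against SD on those numbers. Delete the pointer to the power calculation after the 200, or replace it with an actual AUC precision calculation that names the positive class.

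The change costs a few sentences and no extra patients. The one drawback is a less favourable stated ASD group size. If 200 confirmed ASD cases are in fact intended, the total of 300 cannot stand: at the audit rate about 318 referrals would be needed.

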**Fig. 3 Fig3:**
[figure not shown]
Flow diagram Phase 1 of the ZAQ-study. Patients will undergo clinical evaluation and be divided into 3 groups: Patients with an ASD (Autism Spectrum Disorder) diagnosis, SD (schizotypal Disorder) diagnosis, neither ASD nor SD diagnosis. In parallel and independent from the clinical evaluation, participants will be assessed with the ZAQ schiZotypy Autism Questionnaire), RAADS-R-DK (Ritvo Adult Aspergers diagnostic Schedule – Revised – Danish translation) and SPQ (Schizotypy Personality Questionnaire)

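### Diagnosis is strongly confounded with clinic and selection route, so the pooled ASD-versus-SD AUC can be biased in either direction for use in undifferentiated referrals

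*Protocol article*

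**What the plan says.** Two patient streams enter Phase 1 by different rules (Protocol article, Recruitment and testing). The first 200 patients "will be recruited from the pool referred to the specialised clinic for diagnostic assessment of ASD", so their diagnosis is open at referral. For the second stream, "100 patients will be recruited from the specialised psychosis clinic at Mental Health Centre with an SD diagnosis". No ASD patients are planned from the psychosis clinic. The Abstract describes the first stream differently, as 200 autistic patients.

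On the reference diagnosis the article says:

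- Recruitment and testing, main text: "the diagnostic assessment will be carried out as usual and will follow gold standard guidelines in their respective fields". The DSM-5 interviews, the Adult Asperger Assessment (AAA) and the multidisciplinary meeting are then described for ASD.
- Table 3, under a heading that covers ASD and non-ASD psychiatric patients: completion of the AAA, a DSM-5 evaluation and "A conclusion based on multidisciplinary consensus" are inclusion criteria.
- Fig. 3 legend: patients are evaluated and then sorted into three groups. It adds: "In parallel and independent from the clinical evaluation, participants will be assessed with the ZAQ".

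The section on concurrent validity and screening accuracy sets the ZAQ estimate against the diagnostic outcome by logistic regression and a ROC curve, with K-fold cross-validation. The Outcome section sets AUC ≥ 0.7 for ASD versus SD. The post-hoc section also evaluates each item against the diagnostic outcome. The Discussion places the tool's use before referral to either kind of clinic.

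**The concern.** An SD patient in this sample will usually differ from an ASD patient in three ways at once: the diagnosis, the clinic, and the route into the study (selected on an established diagnosis rather than referred with an open question). A ZAQ score or item that tracks the second or third difference is credited with discriminating the first. In the intended setting the patient has not yet been sorted into a clinic, and those differences are absent.

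Two things are at stake. One is whether a pooled AUC at or above 0.7 supports use at referral. The other is the content of the shortened ZAQ, because items are to be kept or given more weight on the same contrast. K-fold cross-validation guards against overfitting. It does not help here, because the association between clinic and diagnosis is carried into the training and the testing parts alike.

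Separately, the statements on the reference assessment do not fit together. Patients recruited because they already hold the diagnosis are not obviously patients who are evaluated within the study and then sorted. Assessment as usual in each field is also not obviously the AAA, DSM-5 and consensus package that Table 3 asks of everyone.

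**Working it through.** **The plan's own figures.** The sample of 500 over 60 items gives 500/60 = 8.3, which agrees with the stated 8:1. That calculation concerns factor structure. The article gives no precision for the AUC, so there is no stated figure to reproduce on this point.

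**Expected SD patients by clinic.** The inputs are the 200 referrals and the Background audit: "about 37% of the adults referred to our clinic for the assessment of ASD, did not meet diagnostic criteria", and almost 40% of those were on the schizophrenia spectrum, mainly with SD.

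- Without ASD: 200 × 0.37 = 74. With ASD: 200 − 74 = 126.
- Schizophrenia spectrum: 74 × 0.40 = 29.6, about 30. This is an upper bound for SD.
- Share of SD patients from the psychosis clinic: w = 100/129.6 = 0.772. If only half of the spectrum cases are SD (assumption), w = 100/114.8 = 0.871. On the Abstract's wording, w = 1.

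**How strong the confounding is.** With no ASD patients from the psychosis clinic, clinic label alone separates SD from ASD with AUC = w + 0.5(1 − w). This is 0.772 + 0.114 = 0.89 at the lower share and 0.871 + 0.065 = 0.94 at the higher.

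**What an assumed clinic effect does.** Take an equal-variance binormal score with within-clinic AUC A, so d = √2 · Φ⁻¹(A). Let c be a score shift, in standard deviations, that affects only the psychosis-clinic patients. Then

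pooled AUC = w · Φ((d + c)/√2) + (1 − w) · A, with w = 0.772.

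| A | d | c | Φ((d + c)/√2) | Pooled AUC |
|---|---|---|---|---|
| 0.65 | 0.545 | +0.2 | 0.701 | 0.69 |
| 0.65 | 0.545 | +0.3 | 0.725 | 0.71 |
| 0.65 | 0.545 | −0.3 | 0.569 | 0.59 |
| 0.70 | 0.742 | +0.3 | 0.769 | 0.75 |

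The values of c are assumptions. The document gives neither size nor sign.

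**Precision of a within-clinic AUC.** Hanley-McNeil at A = 0.70: Q1 = A/(2 − A) = 0.538 and Q2 = 2A²/(1 + A) = 0.576. The variance is [A(1 − A) + (n_SD − 1)(Q1 − A²) + (n_ASD − 1)(Q2 − A²)]/(n_SD · n_ASD).

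- 30 SD versus 126 ASD: SE 0.057, 95% CI 0.59 to 0.81.
- 15 SD versus 126 ASD: SE 0.079, 95% CI 0.55 to 0.85.
- Pooled, 130 SD versus 126 ASD: SE 0.033, 95% CI 0.64 to 0.76.

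**The case against.** Phase 1 is a development phase, validation is reserved for an independent Phase 2 sample, and a subgroup AUC is the kind of detail that an analysis plan may hold. That is fair as far as it goes. The confounding, however, comes from the recruitment that the article itself fixes. Phase 2 does not remove it either, because the items it tests will have been chosen on this contrast.

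Several stronger readings are tempting, and the document does not support them:

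- **That the AUC is inflated.** Nothing fixes the sign of a clinic effect, and the -0.3 row of the table shows it can go the other way.
- **That a 0.2 shift carries 0.65 to the threshold.** Applying the shift to every SD patient gives 0.70 (and takes 0.70 to 0.77 at +0.3). This holds only if the ASD clinic yields no SD patients at all.
- **That clinic and diagnosis coincide completely.** Up to about 30 SD patients are expected among the ASD-clinic referrals, so the confounding is partial.
- **That SD patients answer knowing their diagnosis and ASD patients do not.** The timing of ZAQ is not settled. Table 3 makes a completed consensus conclusion an inclusion criterion for all patients, so ASD patients may also know theirs. Independence in the Fig. 3 legend may mean only that assessors do not use the ZAQ result.
- **That SD is diagnosed by ICD-10 in this study and ASD by DSM-5.** The sentence "The diagnosis can be made if at least 4 out of 9 ICD-10 criteria are met" is background on the disorder, not a stated study reference standard. Taken at face value, Table 3 requires one assessment of all patients.

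The remedy also has limits. The illustrated gaps between pooled and within-clinic AUC (0.04 to 0.06) are no larger than about one within-clinic SE.

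**Conclusion.** The point holds as a design limitation that the plan should address. At the audit rates, about 77% or more of SD patients come from another clinic and were selected on an existing diagnosis, while all ASD patients come from ASD-clinic referrals. The pooled AUC, and the item selection that uses the same contrast, can therefore be biased in either direction relative to the intended use. Under the assumed shifts of 0.2 to 0.3 standard deviations the change is roughly 0.04 to 0.06 in AUC, enough at +0.3 to move 0.65 past the 0.7 threshold.

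This rests on the audit rates carrying over to the study, on a binormal score and on the assumed shift. Whether the diagnostic methods actually differ between the groups cannot be decided from the article. What can be said is that Table 3, the recruitment text and the Fig. 3 legend are not reconciled. Even with a common assessment, the confounding with clinic and selection route would remain.

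**What to change.** 1. Prespecify, beside the pooled AUC, the ASD-versus-SD AUC among the ASD-clinic referrals as a secondary estimate with its confidence interval.
2. Label the pooled AUC as a two-clinic estimate, and do not rest claims about use at referral on it alone.
3. Reconcile Table 3 and the Fig. 3 legend with the recruitment text. State which assessment psychosis-clinic patients have completed, and when ZAQ is answered relative to the diagnostic conclusion, for each stream. Align the Abstract's 200 autistic patients with the 200 referrals.

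The cost is wording and one additional analysis, with no new patients or assessments. The drawback is imprecision. With at most about 30 SD patients in the ASD clinic the secondary estimate can reveal only a large gap, and with 15 even less, so it is supportive rather than decisive. If the Abstract's wording is the intended one, the ASD clinic would contribute no SD patients and the estimate could not be formed. That is a further reason to settle the wording first.
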